### Sample size {14}

The sample size required for the primary outcome was established to provide adequate power to detect half an MCID difference (15.3/2) in the FAOS Pain score between the control flat-cut Weil and experimental wedge-cut groups, with an average estimated baseline standard deviation of 20.8. The MCID and baseline SD were derived from a previous study [15], and 0.5MCID was determined to be a clinically important effect that would influence future clinical decision-making regarding technique selection. A mixed-effects model (analysis of covariance (ANCOVA)) was selected as the most appropriate to answer the question posed, with power (*β*) at 0.9 and *α* of 0.05, with an allowance for a dropout rate of 10%. The required sample size was determined using GPower [18] to be *N* = 80 patients, with patient age at surgery, sex, body mass index, single/multiple procedures and adjunct procedures included as model covariates.

The sample size required for the secondary outcome was established to provide adequate power to detect a 15% reduction in complication incidence from a baseline of 60% incidence. The reduction in incidence was deemed to be the minimal amount of improvement that would influence future decision-making regarding technique selection in this patient population. A one-sided test within a logistic regression model was selected within GPower, with the *R*^2^ for other predictors in the model (patient age at surgery, sex, body mass index, single/multiple procedures and adjunct procedures) set to 0.1. The required sample size was determined to be *N* = 123 procedures.

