### Recruitment {15}

The principal investigator for the study performed a total of 127 Weil osteotomies in 87 patients over the 12 months preceding the study. To meet the required sample size of *N* = 80 patients with *N* = 123 procedures to assess the primary and secondary outcomes, respectively, the expected recruitment period will extend over 12 months. All prospective patients eligible for recruitment will be approached to participate in the study.

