#### Secondary outcome analysis

The secondary outcome of the trial will be the incidence of procedure-specific complications by the end of the follow-up period (12 months). A binary logistic regression will be used to assess the effect of intervention allocation on complications incidence in a multivariable model containing confounders described above. Alpha will be set at 0.05 and partial eta^2^ used to assess model fit. Odds ratios with 95% confidence limits will describe the strength and direction of relationships between model predictors and the probability of having a complication compared to not having one.

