## Discussion

The trial will provide clinical data pertaining to the efficacy of the modified wedge-cut Weil osteotomy procedure compared to the traditional flat-cut method. Flat-cut Weil osteotomy is a routinely performed procedure with complications frequently reported [1, 5, 6]. The wedge-cut modification purportedly has functional and mechanical advantages over the flat-cut technique; however, in vivo data and quality of evidence are currently lacking [11, 26].

A previous study reported satisfactory performance on the American Orthopaedic Foot and Ankle Society (AOFAS) forefoot score (with 65% of patients reporting no pain and 23% reporting mild pain), but higher than expected complication rates for transfer metatarsalgia, floating toes, infection and wound healing complications in patients receiving segmental resection (wedge-cut) osteotomies [11, 26]. The study, however, was a retrospective case series, lacking baseline data and with a short (minimum 6 months) follow-up. To the best of the authors’ knowledge, the current trial will be the first to directly examine the clinical efficacy of the wedge-cut Weil osteotomy within a randomised control design.

Quality assurance of the trial will be maintained through regular auditing and reporting on data completeness, consistency and validity. The trial has been designed in accordance with the Standard Protocol Items: Recommendations for Interventional Trials (SPIRIT) 2013 guidelines, in order to enhance transparency and facilitate appraisal of its scientific merit, ethical considerations, and safety aspects [27].

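### The secondary sample size of 123 procedures does not follow from its stated inputs and gives about 50% power or less, not adequate power, for a fall in complications from 60% to 45%

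*Protocol article*

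**What the plan says.** Sample size {14} sets a separate target of 123 procedures for the secondary outcome, procedure-specific complications up to 12 months. It says this number gives "adequate power to detect a 15% reduction in complication incidence from a baseline of 60% incidence" and describes the reduction as the smallest that would change the choice of technique. On method it says "A one-sided test within a logistic regression model was selected within GPower", with the R-squared for age, sex, body mass index, "single/multiple procedures and adjunct procedures) set to 0.1". It gives no power value for this outcome; the only one in the section belongs to the primary outcome: "with power (*β*) at 0.9 and *α* of 0.05, with an allowance for a dropout rate of 10"%.

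Secondary outcome analysis specifies a binary logistic regression: "Alpha will be set at 0.05 and partial eta^2^ used to assess model fit". It adds that "Odds ratios with 95% confidence limits will describe the strength and direction of relationships" between the predictors and the probability of a complication. Trial design {8} sets 1:1 allocation, and Sequence generation {16a} randomises participants, not procedures.

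Recruitment {15} reports that the principal investigator "performed a total of 127 Weil osteotomies in 87 patients over the 12 months preceding the study", and it names 80 patients and 123 procedures as the two required sample sizes.

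**The concern.** A difference of 15 percentage points near the middle of the probability scale usually needs well over 100 units per arm, so 123 in total looks too small. Complications are the only secondary outcome and form half of the study's stated aim. A reader told that this comparison was adequately powered could take a non-significant odds ratio as evidence that the two techniques have similar complication rates. If true power is near one half or lower, a real difference of the size the protocol calls decision-relevant would be missed about as often as it was found, or more often.

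Three further points affect how the figure should be stated. The text does not say whether the 15% is absolute or relative. The planning is one-sided, while the reported limits are the usual 95% ones. Procedures are counted as the units although patients are randomised.

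**Working it through.** **Inputs.** From Sample size {14}: control rate p1 = 0.60, a 15% reduction, a one-sided test, R-squared 0.1, stated N = 123. From Secondary outcome analysis: alpha 0.05. From Trial design {8}: 1:1 allocation, so treatment is a binary predictor with half the units in each arm. Assumed: p2 = 0.45 (absolute reading), power 0.80 as benchmark, and 0.90 as used for the primary outcome.

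**Attempt to reproduce 123.** Pooled two-proportion formula:

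N = 2 × [z(α)·√(2·p̄·q̄) + z(β)·√(p1q1 + p2q2)]² / (p1 − p2)², divided by (1 − R²).

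Here p̄ = 0.525, √(2 × 0.525 × 0.475) = 0.7062, and √(0.24 + 0.2475) = 0.6982.

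- One-sided, 80%: 1.645 × 0.7062 + 0.842 × 0.6982 = 1.749; 2 × 1.749² / 0.0225 = 272; 272 / 0.9 = **302**.
- One-sided, 90%: 1.162 + 1.282 × 0.6982 = 2.056; total 376; 376 / 0.9 = **418**.
- Two-sided, 80%: 1.960 × 0.7062 + 0.588 = 1.972; total 346; 346 / 0.9 = **384**.

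The 123 is not reproduced. The most lenient of these totals, 272 with no allowance for R-squared, is 2.2 times as large.

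**Cross-check on the log-odds scale.** The log odds ratio is ln(1.5) − ln(0.45/0.55) = 0.606. N = 2 × (1/0.24 + 1/0.2475) × (1.645 + 0.842)² / 0.606² / 0.9 = 307, in line with 302.

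**Power at 123.** Power = Φ{[0.15·√n − z(α) × 0.7062] / 0.6982}, with n per arm equal to 61.5, or to 61.5 × 0.9 = 55.35 after the R-squared allowance.

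| | R² = 0 | R² = 0.1 |
|---|---|---|
| One-sided | Φ(0.021) = 0.51 | Φ(−0.065) = 0.47 |
| Two-sided | Φ(−0.298) = 0.38 | Φ(−0.384) = 0.35 |

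**If the 15% is relative.** p2 = 0.60 × 0.85 = 0.51. The one-sided 80% requirement becomes 752 / 0.9 = about 835, and one-sided power at 123 is 0.24 (R² = 0.1) to 0.26 (R² = 0).

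**Detectable difference at 123.** With R² = 0.1, one-sided power is 0.79 for a 23-point fall and 0.82 for a 24-point fall, so 80% is reached at about 23 to 24 points. Two-sided, a 26-point fall (p2 = 0.34) gives Φ{[0.26 × 7.440 − 1.960 × 0.7058] / 0.6815} = 0.79.

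**Clustering.** At 127/87 = 1.46 procedures per patient, the design effect is approximately 1 + 0.46 × ICC. The documents give no within-patient correlation. Over an assumed range of 0.1 to 0.5 the design effect is 1.05 to 1.23, and one-sided power at 123 (R² = 0.1) falls from 0.47 to between 0.46 and 0.41.

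**Expected yield.** 80 × 127/87 = 117 procedures; 123 × 87/127 = 84.3, so about 85 patients for 123. At 117 procedures, two-sided power is 0.34 (R² = 0.1) to 0.37 (R² = 0).

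**The case against.** The main defence is that the protocol states no power for this outcome, so an 80% benchmark is imported. That is true and should be said, but it does not rescue the claim: power of about one half is not adequate on any usual reading, and at the 90% used for the primary outcome the gap is wider. Taking the 15% as absolute already favours the protocol.

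Four stronger readings are tempting and are not supported.

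- **That 80 patients cannot supply 123 procedures.** The ratio of 1.46 is one surgeon's previous year, while the trial has several participating surgeons. The gap (117 against 123) is about 5%. Plans for assessment and collection of outcomes {18a} lets data collection run until the minimum sample sizes are met, and Recruitment {15} gives 123 as a requirement, not a forecast. The shortfall is an expectation, not a contradiction.
- **That one-sided planning is an error in itself.** The secondary objective is directional (fewer complications with wedge-cut) and the trial is a superiority trial. What stands is a mismatch: 95% limits correspond to a two-sided 5% test, so one-sided power overstates what the reported interval can show.
- **That the Discussion shows wedge-cut to be worse.** It cites "higher than expected complication rates for transfer metatarsalgia, floating toes, infection and wound healing complications in patients receiving segmental resection (wedge-cut) osteotomies", but the protocol itself describes that source as a retrospective case series without baseline data and with short follow-up, and shows no comparison with flat-cut. It gives little support for an effect in the other direction.
- **That the origin of 123 can be identified.** If treatment is entered as a normally distributed predictor, quite different settings land nearby: 122.7 with 95% power and R² = 0, and 124.2 with a two-sided test, 80% power and R² = 0.1. The documents do not say which settings were used, and the finding does not depend on it.

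It is also fair that this is a secondary outcome and that the primary target of 80 patients is calculated separately. This point does not touch that calculation.

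**Conclusion.** The statement that 123 procedures give adequate power is wrong as written. On the stated inputs, with the 15% taken as absolute, 123 is about 40% of the 302 procedures needed at 80% one-sided power (123/302 = 0.41). The power ranges in the working are upper figures, because they treat procedures as independent. The conclusion rests on binary 1:1 allocation, alpha 0.05 and the absolute reading. It does not depend on the choice of 80% as benchmark, and the relative reading makes it worse. The patient-to-procedure mismatch is a smaller, secondary point that rests on one year's case mix.

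**What to change.** In Sample size {14}:

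1. Say whether the 15% is absolute or relative.
2. Replace the claim of adequate power with the actual power at 123 procedures (for 60% against 45% with R² = 0.1: about 47% one-sided and 35% two-sided, before clustering), or with the detectable difference (about 23 to 24 points at 80% one-sided power).
3. Give the power on a two-sided basis, to match the 95% limits in Secondary outcome analysis.
4. Describe the complication comparison as estimation, an odds ratio with its 95% confidence interval, and not as a powered test.

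In Recruitment {15}, keep 123 labelled as a target and add that, at the previous year's ratio of 127/87, 80 patients are expected to give about 117 procedures and about 85 patients would be needed for 123.

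The cost is wording and a less favourable stated figure. No extra patients are required.

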## Statistical methods

### Statistical methods for primary and secondary outcomes {20a}

#### Principles

An analyst blinded to treatment allocation will perform the primary and secondary analyses, by comparing the intervention group to the control group. Data will be analysed following intention-to-treat principles (i.e. participants will be analysed in the group to which they were randomised to). Data normality of baseline characteristics and process measures will be evaluated by visual inspection of histograms. Continuous variables will be presented as means and standard deviations for normally distributed variables: median, minimum, maximum and interquartile range for non-normally distributed variables. Frequencies and percentages will be used to summarise categorical variables. Percentages will be calculated using the number of participants for whom data are available as the denominator. Alpha will be set at 0.05 and effect sizes as described in the sample size calculation will be considered of interest.

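### The complication outcome is sized with a one-sided test but reported with 95% limits at an alpha of unstated sidedness, and 123 procedures do not give adequate power on either basis

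*Protocol article*

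**What the plan says.** The second paragraph of Sample size {14} opens: "The sample size required for the secondary outcome was established to provide adequate power". The target is a 15% reduction from a 60% complication incidence, with R² for the other predictors set to 0.1 and a result of 123 procedures. On the test it says: "A one-sided test within a logistic regression model was selected within GPower". It gives neither an alpha nor a power figure for this outcome. The only alpha in the section belongs to the primary outcome: "with power (*β*) at 0.9 and *α* of 0.05, with an allowance for a dropout rate of 10" per cent.

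The analysis text gives an alpha but no sidedness. Under Principles: "Alpha will be set at 0.05 and effect sizes as described in the sample size calculation will be considered of interest". Under Secondary outcome analysis: "Alpha will be set at 0.05 and partial eta^2^ used to assess model fit". That section then specifies the reporting: "Odds ratios with 95% confidence limits will describe the strength and direction of relationships between model predictors and the probability of having a complication".

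The secondary objective in Objectives {7} is directional: it asks whether the wedge cut has fewer complications.

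**The concern.** The protocol fixes sidedness only in the sample size, where a one-sided test lowers the required number. In the analysis it names an alpha and an interval without saying which test they serve. A one-sided 5% test pairs with a 90% interval. A conventional 95% interval pairs with a two-sided 5% test, or a one-sided 2.5% test.

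The false-positive rate for a claim of fewer complications with the wedge cut is therefore 5% if the one-sided test carries over at 0.05, and 2.5% if the 95% limits are the guide. As the text stands, that choice could be made after the data are seen. The sidedness also sets how much power the 123 procedures provide, and the protocol calls that power adequate without giving a figure.

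**Working it through.** **Inputs.** From Sample size {14}: 60% control incidence, 15% reduction, R² = 0.1, one-sided test, N = 123 procedures. From Trial design {8}: 1:1 allocation. From Principles and Secondary outcome analysis: alpha 0.05 and 95% limits.

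**Assumptions.** The sizing test used alpha 0.05, the only alpha stated for this outcome. The reduction is taken as absolute (60% vs 45%) or relative (60% vs 51%), because the text does not say which. Power of 80% or 90% is tried for the sample size. Procedures are treated as independent.

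**1. The plan's own figure.** The Hsieh formula for a binary 1:1 predictor, with P the mean of the two rates, is

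N = [z_α·√(P(1−P)/0.5) + z_power·√(p₁q₁ + p₂q₂)]² / [(p₁−p₂)²·0.5] / (1−R²)

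For 60% vs 45%, P = 0.525. One-sided at 80% power:

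[1.645 × 0.706 + 0.842 × 0.698]² / (0.0225 × 0.5) / 0.9 ≈ 303

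| Test at 0.05 | 80% power | 90% power |
|---|---|---|
| One-sided | 303 | 418 |
| Two-sided | 384 | 513 |

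The stated 123 is not reproduced. It is approached if allocation is entered as a standard-normal predictor (Demidenko, variance-corrected): about 120 one-sided at 90% power. Two-sided normal-predictor variants also come close (about 123 at 85% power with the correction, about 125 at 80% without it). The number 123 therefore does not show which sidedness was used.

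**2. Where the two readings part.** They part for z between 1.645 and 1.960 in favour of the wedge cut. Take 62 and 61 procedures with 37/62 (60%) on flat cut. The log odds ratio has SE = √(1/37 + 1/25 + 1/b + 1/(61−b)), where b is the number of wedge-cut complications. The R² of 0.1 is applied by dividing the SE by √0.9.

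For b = 26:
- OR = (26/35)/(37/25) = 0.50, log OR = −0.689, SE = 0.366.
- z = 1.88, one-sided p = 0.030, 95% limits exp(−0.689 ± 1.96 × 0.366) = 0.24 to 1.03.
- With R² = 0.1: SE = 0.386, z = 1.79, one-sided p = 0.037, limits 0.24 to 1.07.

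For b = 27 (44%, close to the 15-point target):
- OR = 0.54, limits 0.26 to 1.10, one-sided p = 0.044 without adjustment.
- With R² = 0.1: z = 1.62, one-sided p = 0.053. This fails both tests, so nothing is in dispute.

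**3. Power at N = 123**, with 61.5 per arm and R² = 0.1:

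Var(log OR) = [1/(61.5·p₁q₁) + 1/(61.5·p₂q₂)] / 0.9; power = Φ(|log OR|/SE − z_α)

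| Reading of 15% | log OR | SE | log OR ÷ SE (absolute) | One-sided 0.05 | Two-sided 0.05 | Difference |
|---|---|---|---|---|---|---|
| Absolute, 60% vs 45% | −0.606 | 0.385 | 1.574 | 47% | 35% | 12 points |
| Relative, 60% vs 51% | −0.365 | 0.384 | 0.951 | 24% | 16% | 9 points |

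The last column is the chance, if that effect is true, of a result that one reading calls significant and the other does not.

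**The case against.** A reader might infer that the protocol holds two explicit success rules, so that a borderline result passes under one section and fails under the other. The text does not go that far. The sample size gives no alpha for this outcome. The analysis section never says two-sided, and it uses the 95% limits to describe the odds ratios, not to decide. A one-sided 0.05 test printed beside conventional 95% limits fits every sentence. That stands, and it limits the point to unresolved sidedness and a mismatch between test and interval.

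A reader might also infer that the plan would be blind to harm from the wedge cut, since the Discussion cites "higher than expected complication rates for transfer metatarsalgia, floating toes, infection and wound healing complications in patients receiving segmental resection (wedge-cut) osteotomies". This is not supported either. The reported limits would show an excess in either direction, and Interim analyses {21b} provides continual adverse event monitoring in both arms. The cited study, as the Discussion says, is a retrospective case series without baseline data, so it is not a comparison with the flat cut.

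It can fairly be said that a one-sided test suits the directional objective, and that an analysis plan not shown may settle sidedness. A missing detail alone would be no finding. Here, though, the article itself fixes a one-sided test for the sizing, pairs the analysis with an interval that does not match a one-sided 5% test, and claims adequate power.

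**Conclusion.** The point holds as a mismatch to be resolved. The sizing test is one-sided with no stated alpha, the analysis alpha has no stated sidedness, and the 95% limits correspond to a two-sided 5% test. Results with one-sided p between 0.025 and 0.05 are left open to either description. If the planned effect is true, about 12% of trials would land there on the absolute reading and about 9% on the relative one.

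The claim of adequate power at 123 procedures fails on every reading tried for a two-arm factor: 35% or 16% two-sided, and 47% or 24% one-sided at 0.05. Settling the sidedness does not repair the number 123, which is not reproduced for a binary allocation under either test.

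These figures assume alpha 0.05 for the sizing test and independent procedures. The plan expects about 1.5 procedures per patient (123/80) and randomises patients. Positive correlation within patients would lower the power further, but the protocol gives no figure for it. The outcome is secondary, but it is the trial's only secondary outcome and was sized separately, so the correction should be made.

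**What to change.** Use one rule in Sample size {14} and Secondary outcome analysis: test the allocation odds ratio two-sided at 0.05, consistent with the 95% limits already planned. If a one-sided test is preferred, set it at 0.025, which matches the same limits.

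In Sample size {14}, state the alpha for this outcome, say whether the 15% reduction is absolute or relative, and replace the claim of adequate power with the power at 123 procedures on the chosen basis. Under the assumptions above that is about 35% (absolute) or 16% (relative).

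The cost is wording in two sections and a less favourable stated power. No extra patients or data are needed for this change.

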### Recruitment {15}

The principal investigator for the study performed a total of 127 Weil osteotomies in 87 patients over the 12 months preceding the study. To meet the required sample size of *N* = 80 patients with *N* = 123 procedures to assess the primary and secondary outcomes, respectively, the expected recruitment period will extend over 12 months. All prospective patients eligible for recruitment will be approached to participate in the study.

### Assignment of interventions: allocation

#### Sequence generation {16a}

Participants will be randomly assigned to receive either a flat-cut Weil osteotomy (control, group A) or wedge-cut osteotomy (experimental, group B) procedure using a central computer-based simple randomisation system, with a 1:1 allocation without blocking. The random allocation sequence will be embedded within the clinical registry via a randomisation algorithm (Matlab 2018b, Mathworks Inc., USA). The allocation will be communicated electronically to the treating surgeon via an allocation code comprising nondescript terminology, whereby the allocation cannot be inferred from the label to other study personnel.

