## Methods: participants, interventions and outcomes

### Study setting {9}

Patient recruitment and data collection will be performed at the private hospitals and consulting clinics for the participating surgeons (New South Wales, Australia). Recruitment is expected to be complete by April 2023. Patients will be randomly allocated to either intervention using a central computer-based allocation randomisation system prior to surgery. The trial is embedded in a clinical registry with patient, surgical and clinical data captured as part of routine clinical care. Figure 1 outlines the schedule of study activities, and Fig. 2 outlines the study design for the trial described above.

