### Eligibility criteria {10}

Patients presenting to the participating surgeons for treatment of propulsive metatarsalgia who are over 18 years of age and eligible for surgical intervention (having failed a minimum of six months of conservative interventions) will be eligible for recruitment. Patients will need to be registered in the SOFARI registry and provide additional written informed consent for participation in the present randomised controlled trial.

Patients who have declined or revoked consent for use of clinical data for research (for the SOFARI registry or the current trial) or are unable to provide informed consent will be excluded. Patients will additionally be excluded if they have had recent (< 6 months) prior surgery to the affected forefoot, if they require additional procedures involving the soft tissues of the foot-ankle complex, have had their surgery booking cancelled with the participating surgeon or have been judged by the participating surgeons as incapable to complete patient reported outcome measures (PROMs) as required for the study due to psychological impairment or insufficient English language capacity (Fig. 3).

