#### Primary outcome analysis

The primary outcome of the trial is postoperative pain at 12 months follow-up represented by the pain subscale of the FAOS. A mixed-effects ANCOVA will be used to test for differences between the groups with the following factors and covariates included in the model:Patient ID (random factors)Baseline FAOS pain subscore (covariate)Age at surgery (covariate)Sex (covariate)Multiple proceduresAdjunct procedures

The overall model fit will be assessed with partial eta^2^ and coefficients (*β*) with 95% confidence limits will describe the strength and direction of relationships between factors and the postoperative FAOS-Pain score. Post hoc comparisons with Dunnett tests (against control) will be used to compare osteotomy groups. Cohen’s *d* will be used to report the effect size of differences between the groups. A Cohen’s *d* exceeding 0.36 will be deemed clinically significant.

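### Several surgeons operate and allocation is unstratified, but the listed model terms omit the treating surgeon: this costs some precision and leaves chance imbalance uncorrected, without biasing the estimate

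*Protocol article*

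**What the plan says.** **Operators and sites.** Study setting {9} says that recruitment and data collection are "performed at the private hospitals and consulting clinics for the participating surgeons". Eligibility criteria {10} also uses the plural: "Patients presenting to the participating surgeons for treatment of propulsive metatarsalgia". The section on the choice of comparators says that these surgeons use both techniques. The only caseload given is in Recruitment {15}: "The principal investigator for the study performed a total of 127 Weil osteotomies in 87 patients" in the 12 months before the study.

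**Allocation.** Sequence generation {16a} assigns patients "using a central computer-based simple randomisation system, with a 1:1 allocation without blocking". It names no stratification factor. Concealment mechanism {16b} withholds the code from the surgeon until the patient has been recruited on the day of surgery.

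**Models.** Primary outcome analysis fixes the terms: "Patient ID (random factors)Baseline FAOS pain subscore (covariate)Age at surgery (covariate)Sex (covariate)Multiple proceduresAdjunct procedures" (the list items run together in the extracted text). Secondary outcome analysis fits a logistic regression "in a multivariable model containing confounders described above". Sample size {14} gives a similar list, adding body mass index: "with patient age at surgery, sex, body mass index, single/multiple procedures and adjunct procedures included as model covariates". Neither surgeon nor site appears in any of these lists. Figure 4, which the baseline section cites for the confounders, is not in the text available to this review.

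**The concern.** The trial compares two manual techniques, one of which adds a second osteotomy. Plantar plate repair and adjunct procedures are decided case by case. The operator is therefore a plausible source of variation in pain and complications, and is known before allocation. With about 80 patients and simple randomisation, a surgeon's patients can by chance fall unevenly between the arms. If the model has no surgeon term, that imbalance is not corrected, and variation between surgeons stays in the residual. What is at stake is precision in a small trial, and the reader's ability to see who performed which technique.

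**Working it through.** The plan gives no figure for surgeon effects, so there is none of its own to reproduce. Two of its figures are used as they stand: 80 patients and an SD of 20.8 (Sample size {14}). Whether 80 follows from the plan's other inputs is a separate question.

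**Assumptions (not in the documents).** One surgeon performs a share p of cases. That surgeon's patients differ on average by g FAOS-Pain points from the rest. The range taken is p = 0.25 to 0.50 and g = 5 to 10.

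**Formulas.**
- Share of outcome variance due to surgeon: V = p(1−p)g² / 20.8², with 20.8² = 432.64.
- Narrowing of the confidence interval after adjustment: 1 − √(1−V).
- 95% range of the chance shift in the unadjusted estimate: ±1.96 × g × 2√(p(1−p)/80).

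| p | g | V | Narrowing | Chance shift (points) |
|---|---|---|---|---|
| 0.25 | 5 | 4.69/432.64 = 1.1% | 0.5% | ±0.95 |
| 0.50 | 5 | 6.25/432.64 = 1.4% | 0.7% | ±1.10 |
| 0.25 | 10 | 18.75/432.64 = 4.3% | 2.2% | ±1.90 |
| 0.50 | 10 | 25/432.64 = 5.8% | 2.9% | ±2.19 |
| 0.10 | 10 | 9/432.64 = 2.1% | 1.0% | ±1.31 |

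The last row shows one surgeon dominating with a 90:10 split.

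**Check by simulation.** In 200,000 simple randomisations of 80 patients with two surgeons of 40 patients each, one surgeon's share differed between arms by at least 10 percentage points in 44% of runs and by at least 20 in 9%. The 95th percentile of the shift was 1.13 points for a 5-point gap and 2.25 for a 10-point gap, in line with the formula.

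**The shift is part of the usual error.** The unadjusted standard error with 40 per arm is 20.8 × √(2/40) = 4.65, so the 95% half-width is 1.96 × 4.65 = 9.12 points. The surgeon component is (1.90/9.12)² = 4.3% to (2.19/9.12)² = 5.8% of that variance for a 10-point gap, the same figures as V. The chance shift and the variance share are thus one quantity seen two ways. Removing it takes the half-width from 9.12 to about 9.12 × 0.971 = 8.85 at most under these assumptions.

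**Limit of the calculation.** The 20.8 is a baseline SD, used here for the unadjusted outcome. The planned model also adjusts for baseline pain. Surgeon's share of the remaining variance could be larger than V, or smaller if baseline pain already explains part of the gap. The documents do not give the correlation needed to say which. No comparable figure is worked for complications, because nothing bears on how rates differ by surgeon.

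**The case against.** **Randomisation already protects the estimate.** Allocation is individual, central and concealed, so surgeon is balanced in expectation and chance imbalance is ordinary sampling error that the standard error reflects. This stands, and it confines the point to precision and correction of imbalance.

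**The inputs are assumed.** A 10-point gap between surgeons exceeds the 15.3/2 = 7.65-point difference the trial seeks, and nothing in the documents supports it. The principal investigator's own yearly volume (87 patients, 127 osteotomies) exceeds the required 80 and 123, so one surgeon may do most of the work. This also stands, and is why a 5-point gap and a 90:10 split are shown.

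**Figure 4 might include surgeon.** It might, and the complication model's confounders could be read as referring to it. The explicit primary list does not include surgeon, so the figure and the list would then disagree.

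**A main effect does not cover everything.** Differing skill with the second cut is a surgeon-by-technique interaction, which a fixed surgeon term does not remove. That is correct; the tabulation would show how each surgeon's cases divide between techniques, but would not estimate the interaction.

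**Simple randomisation is defensible.** A reader might infer that allocation should move to blocks within surgeon. The documents do not support this as a clear improvement: the surgeons obtain consent and cannot be blinded, and unblocked allocation is the least predictable scheme for them.

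**Conclusion.** The point holds as one of efficiency and transparency. The documents show several surgeons and hospitals, unstratified simple randomisation, and listed model terms without the surgeon. Under assumed gaps of 5 to 10 points and a surgeon share of 25% to 50%, surgeon accounts for about 1% to 6% of outcome variance, and the interval would be up to about 3% narrower after adjustment. The benefit is smaller if one surgeon performs most cases. All of this rests on surgeon numbers, caseloads and effects that are not stated.

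A reader might infer that the trial cannot tell technique from operator. The documents do not support that: with individual concealed allocation, operator does not confound the comparison. Nor should the chance shift be set against the 7.65-point target as if it came on top of the reported uncertainty, since it is already inside it.

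**What to change.** Before any unblinded analysis, prespecify treating surgeon as a fixed factor in the primary mixed model and the logistic model for complications, with a stated rule for pooling very low-volume surgeons. Tabulate technique by surgeon in the report. If Figure 4 includes surgeon, reconcile it with the list under Primary outcome analysis.

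The cost is a few degrees of freedom: one fewer than the number of surgeon categories. The surgeon should be identifiable from the operation reports and intraoperative data the protocol already collects, although it is not named there as a data field. Allocation need not change, so the step remains available after recruitment has closed.
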